### Study design, sample and recruitment

The aims of the study will be evaluated using a quasi-experimental two-group study design, as summarized in
Figure 1. The intervention will constitute an individualized licence to purchase herbal cannabis in selected pharmacies for a duration of 12 months in Berlin, Germany. Control group participants will be recruited in Hamburg, a city comparable to Berlin in terms of sociodemographic indicators (population, deprivation) and user characteristics
^30^.

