### Sample size and data analyses

The study outcomes will be analysed according to ‘Intention-to-treat’ (ITT) principles. Specifically, the sample to be analysed is defined as all users who have provided a usual consumption unit within 4 weeks after completing the baseline questionnaire. Over-recruitment will compensate for participants failing to provide a consumption unit within this period. According to ITT principles, only those participants who provided their baseline data, including their usual consumption unit, will be included in the analyses.

To examine between-group differences with a t-test, the required sample size of this study was calculated assuming a power of 80%, a 5% alpha error, and a THC standard deviation equal to one-third of its mean (approximated using Canadian data,
^43^; adding 25% to account for uncertainty). The required sample size was estimated to sum up to n=698 participants (control: n=349; intervention: n=349) for detecting group differences in THC exposure.

Not relevant for sample size considerations, we expect that 20% (control: 30%; intervention: 10%) of all participants of the ITT sample will be lost to T12 follow-up. Subjects dropping out of the study will not be replaced and missing values will be imputed using the ‘Last Observation Carried Forward‘ (LOCF) technique. The critique regarding LOCF imputation methods
^44^ does not apply to our study, as this method will bias the data towards the null hypothesis (assuming no change over time) and therefore representing a conservative imputation approach. The assumptions of LOCF will be examined in sensitivity analyses using advanced multiple imputation techniques.

To evaluate both aspects of the primary outcome, two analyses need to be conducted. First, the THC exposure levels in the past 30 days ascribed to illegal cannabis acquisition within the intervention group needs to be compared between baseline and intervention, with a 50% reduction denoting the minimum threshold for a positive evaluation. Second, a between-group comparison of THC exposure in the past 30 days at T12 adjusting for baseline data will be conducted using a t-test. The dependent variable will be calculated as follows:

$$THC_{T12–adjusted}=\frac{THC_{T12}*100}{THC_{T0}}$$

The actual between-group comparison will be evaluated against the following condition:

$$THC_{T12–adjusted–interventiongroup}<=0.9*THC_{T12–adjusted–control\;group}$$

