Multilevel regression analyses will be performed additionally for evaluating the primary outcome, which serve to rule out the impact of possibly confounding variables. For evaluating the secondary outcomes, the proposed analyses (correction for baseline values, comparison via t-test, confirmation via multilevel regression analyses) will be performed analogously.

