### Limitations

There are several limitations of this study. First, given a lack of randomization, causal inferences cannot be drawn from the study findings without controlling for relevant confounders. We have sought to include a broad variety of questionnaires to capture information on all possible determinants; however, we cannot rule out that some important confounding variables will not be assessed or be biased through self-report. Further, resin will not be part of the dispensary model for it is not available from medical suppliers. As far as we know, resin cannot be prescribed for medical purposes despite favourable THC/CBD ratios (for Dutch data, see
56). For cannabis users preferring resin over herbal cannabis, study participation may therefore be unattractive, and this may bias the study sample towards predominant herbal cannabis users.

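### Aspect 2 of the primary outcome is decided by a t-test adjusted only for baseline THC; the planned confounder-adjusted regression does not enter the success rule

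*Protocol article*

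**What the plan says.** All references are to the Protocol article.

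- **Study design, sample and recruitment.** The design is not randomised: "The aims of the study will be evaluated using a quasi-experimental two-group study design". There is one city per arm: "Control group participants will be recruited in Hamburg, a city comparable to Berlin in terms of sociodemographic indicators". Participants in both cities are volunteers found through posters, consumer groups and local stakeholders.
- **Sample size and data analyses.** For the second aspect of the primary outcome, "a between-group comparison of THC exposure in the past 30 days at T12 adjusting for baseline data will be conducted using a t-test". The outcome is T12 THC × 100 / T0 THC. Then: "The actual between-group comparison will be evaluated against the following condition", namely adjusted THC in the intervention group at most 0.9 times that in the control group. The sample size of 349 per group is also calculated for a t-test.
- **Same section, on confounding.** "Multilevel regression analyses will be performed additionally for evaluating the primary outcome, which serve to rule out the impact of possibly confounding variables". For secondary outcomes the analogous sequence is given as "correction for baseline values, comparison via t-test, confirmation via multilevel regression analyses".
- **Primary outcome.** Overall success needs both aspects to be positive. The adjusted model is not mentioned in that rule.
- **Limitations.** Because there is no randomisation, "causal inferences cannot be drawn from the study findings without controlling for relevant confounders".

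**The concern.** The sample size, the outcome formula and the success condition all attach to the ratio t-test. Its only adjustment is division by each participant's own baseline THC. That deals with baseline exposure in one particular way. It does not balance other determinants of change, and it does not remove differential regression to the mean if the two groups start at different levels of use.

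Such differences are plausible. Only Berlin volunteers gain legal access, so the reason to join differs by city. The Limitations section expects participation to be unattractive to people who prefer resin, because resin is not dispensed; that reason bears on the Berlin offer. The expected loss to follow-up (30% control, 10% intervention) shows that the authors also expect the arms to behave differently.

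The analysis that addresses measured confounding stands beside the success rule, not inside it. If it disagrees with the t-test, the stated rule still follows the t-test. The study is meant to inform legislation, and its economic evaluation is applied to Germany as a whole, so bias in the deciding estimate matters.

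**Working it through.** **1. The plan's own figure.** The protocol states 349 per group. With a 10% difference, two-sided 5% alpha and 80% power, n per group = 2 × (SD/0.10)² × (1.960 + 0.842)²:

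- SD = 1/3 of the mean: 175
- SD = 1.25/3 = 0.4167: 273
- SD = √2/3 = 0.4714: 349

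The stated figure is reached only with a factor √2 that the text does not give. That is a separate matter and is not evidence for this point. It is used here only to fix a range of SDs (1/3, 0.4167, 0.4714).

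**2. Case-mix illustration (all inputs assumed; the documents give none).** No intervention effect. In both cities heavy users drift to 90% of baseline and light users to 110%. Heavy users are 60% of Berlin and 40% of Hamburg volunteers.

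- Berlin mean: 0.6 × 0.90 + 0.4 × 1.10 = 0.98
- Hamburg mean: 0.4 × 0.90 + 0.6 × 1.10 = 1.02
- Ratio: 0.98 / 1.02 = 0.961, about 4 of the 10 points required

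**3. Chance that this alone meets the stated condition**, read as a point estimate. The contrast is Berlin mean − 0.9 × Hamburg mean.

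- Expected value: 0.98 − 0.9 × 1.02 = 0.062
- SE = SD × √((1 + 0.9²)/349) = SD × √(1.81/349)

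| SD | SE | z = 0.062/SE | P(condition met) |
|---|---|---|---|
| 1/3 | 0.0240 | 2.58 | 0.5% |
| 0.4167 | 0.0300 | 2.07 | 1.9% |
| 0.4714 | 0.0339 | 1.83 | 3.4% |

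**4. Shift of the effective threshold.** The true ratio at which the biased estimate sits exactly on 0.9 is 0.9 / 0.961 = 0.937, a true reduction of 6.3%. With this case mix, such an effect meets the condition 50% of the time. Without bias the distance is 0.937 − 0.9 = 0.037, so z is 1.53 (SD 1/3) to 1.08 (SD 0.4714), and the chance is about 6% to 14%.

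**5. The opposite direction.** Reverse the mix, with heavy users 40% of Berlin and 60% of Hamburg. The ratio under no effect is 1.02 / 0.98 = 1.041, and the true reduction needed for a 50% chance becomes 1 − 0.9/1.041 = 13.5%. A true 10% reduction, which meets the condition 50% of the time without bias, gives 0.9 × 1.02 − 0.9 × 0.98 = 0.036. Then z is 1.50 to 1.06, and the chance falls to about 7% to 14%.

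**6. Precision after the fix.** For a covariate-adjusted comparison, n = n(t-test) × (1 − R²) × VIF, where VIF measures how strongly the covariates are related to city. Both inputs are assumptions. From 349 per group: R² = 0.3 and VIF = 1.1 gives 269; R² = 0.2 and VIF = 1.25 gives 349; R² = 0 and VIF = 1.25 gives 437. Precision may improve or worsen.

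**The case against.** **An adjusted model is planned.** Assessment details says questionnaire data are collected partly to control for confounders, the analysis section names multilevel regression for the primary outcome, and Limitations makes causal claims conditional on such control. Read together, the protocol does not say that its causal conclusion will rest on the t-test alone. This stands. The defect is one of hierarchy, not an absent analysis, and calling the t-test unadjusted would ignore the division by baseline.

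**A reader might infer a false-positive rate of 20% to 35%.** In the illustration above, the t-test rejects equality in favour of the intervention with probability 0.35 (SD 1/3) or 0.20 (SD 0.4714). The documents do not support using these as rates of false success: the comparison is judged against the 0.9 condition, which this bias meets in only 0.5% to 3.4% of cases. Aspect 1 must succeed as well.

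**Berlin and Hamburg are described as comparable, including in user characteristics.** That concerns the cities. It does not show that the volunteers are alike, but neither do the documents show that they differ. The correct statement is that they may.

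**Some of this belongs in an analysis plan.** The covariate list does, and its absence is no finding. Which analysis carries the success condition is already fixed in the article.

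**The remedy is partial.** True: with one city per arm, no model separates a city trend from the intervention. Adjustment still reduces bias from measured differences between participants.

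**Conclusion.** The point holds as a matter of hierarchy. The estimate that decides aspect 2 is adjusted for nothing but baseline THC, in a design for which the protocol itself asks for control of confounders, and the model that supplies that control has no place in the success rule.

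The size depends on assumed inputs. A 60/40 against 40/60 case mix with drift to 90% and 110% moves the ratio by about 4 of the 10 points. It rarely creates success from nothing, but it lowers the true reduction that passes half the time from 10% to about 6%, or raises it to about 13.5% if the imbalance runs the other way. The stronger inference, that the study's conclusion is necessarily confounded or that its success rule has a false-positive rate of 20% or more, is not supported. The claim that regression can rule out confounding is too strong under any hierarchy with one city per arm. Severity: should fix.

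**What to change.** - Make the primary analysis of aspect 2 a regression of T12 THC on group, baseline THC as a covariate, and baseline confounders already collected (for example use frequency, CUDIT-R, sociodemographics, tobacco and alcohol use, BSI-18, social situation). The exact list can go in the analysis plan.
- Apply the 10% criterion to the adjusted group effect, expressed as a ratio so that the 0.9 condition carries over. Name this effect in the overall success rule.
- Report the t-test on T12/T0 as supportive. This also settles in advance which result holds if the two disagree.
- Replace the statement that regression rules out confounding: measured confounders are adjusted for, and city-level effects cannot be separated from the intervention with one city per arm.

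The cost is a change of wording and a little more analysis work. The model and the data are already planned. Some precision may be lost if the covariates are strongly related to city.

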### Adverse events and stoppage

If more than 60% of the intervention group participants drop out within the first three months, the study will be stopped immediately, because it will be taken as an indicator for subjects not accepting the administration model.

In addition, the Data Safety Monitoring Board (DSMB) will be formed by pharmacists and social workers working in the addiction and youth protection field. As stipulated in Good Clinical Practice guidelines, the DSMB, as an independent and multidisciplinary group will be established to review, at intervals, accumulating trial data, in order to monitor the progress of the trial and to make recommendations on whether to continue, modify or stop the trial for safety or ethical reasons.

Adverse events will be closely monitored and documented. Criteria have been pre-specified to define a preterm stop to the study. Further, the study team will be in close contact with the participating pharmacies in order to capture all events not foreseen at study inception. In regular meetings, the DSMB will evaluate the progress of the study and may decide to stop the study.

### Economic evaluation

In a ‘cost-benefit-analysis’ (CBA), the proposed dispensary model will undergo an additional economic evaluation, in which the economic benefits from attenuated THC exposure will be contrasted to the programme costs
^52^, with estimates applied to Germany as a whole. Building on the approach of a previous CBAs for Australia
^53^ and using the extended framework of generalized cost-effectiveness analyses
^54^, we will compare the following scenarios:

Null scenario: no implementation of cannabis-specific measures (i.e., no police enforcement, no treatment of cannabis use disorders)
Status quo: implementation of random traffic controls to reduce THC-impaired driving and psychosocial interventions for cannabis use disorders
Dispensary model: as ‘status quo’ but with legal sale of herbal cannabis in pharmacies

For the CBA, the so-called net social benefit will be calculated as the difference between projected costs and benefits discounted over the study period. On the cost side, we will consider all economic costs that can be ascribed to cannabis-related law enforcement, treatment of cannabis use disorders and cannabis-attributable diseases (e.g. psychoses), loss of productivity, and all costs pertaining to establishing and maintaining the dispensary model. On the benefit side, we will consider all economic benefits arising in the following domains: reductions in law enforcement and health-care costs, as well as increases in productivity. Based on the CBA results, a cost-utility-analyses will additionally be conducted by estimating the costs required to avoid one ‘disability adjusted life year’ (DALY
^55^) for the scenario of a nationwide implementation of the dispensary model.

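### The cost-benefit analysis lists law enforcement, health care and productivity as both costs and benefits, contrary to its opening sentence; applied literally between scenarios, savings count twice

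*Protocol article*

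**What the plan says.** All of the relevant text is in the Economic evaluation section of the protocol article.

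- **Opening contrast:** "the economic benefits from attenuated THC exposure will be contrasted to the programme costs".
- **Definition:** "the so-called net social benefit will be calculated as the difference between projected costs and benefits discounted over the study period".
- **Cost side:** "all economic costs that can be ascribed to cannabis-related law enforcement, treatment of cannabis use disorders and cannabis-attributable diseases", then "loss of productivity, and all costs pertaining to establishing and maintaining the dispensary model".
- **Benefit side:** "reductions in law enforcement and health-care costs, as well as increases in productivity".
- **Comparison:** "we will compare the following scenarios". The three are a null scenario (neither enforcement nor treatment of use disorders), the status quo, and the status quo plus pharmacy sale.

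The results are to be applied to Germany as a whole. A cost-utility analysis, giving a cost per DALY avoided, is to be built on them.

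**The concern.** Each of the three benefit domains is already on the cost side, and the cost items are worded as totals, not as changes. A fall in enforcement spending, for example, lowers the cost total under the dispensary model and also qualifies as a benefit. Nothing in the section says that an item entered on one side is left out of the other.

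The opening sentence describes a different account, in which benefits are weighed against programme costs alone and nothing overlaps. The section therefore gives two incompatible descriptions of what goes on the cost side.

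At stake is the sign of the economic result. Doubling the savings favours the dispensary model, and the article's Conclusion expects the economic results to serve as an argument for regulated legalization.

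**Working it through.** The section contains no monetary figure, so there is nothing to reproduce. The check is one of accounting.

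**Notation**
- L_sq, L_d: combined enforcement, health-care and lost-productivity burden under the status quo and under the dispensary model.
- S = L_sq − L_d: the saving.
- P: programme cost (zero under the status quo).
- Net social benefit (NSB) is taken as benefits minus costs. Each saving counted once gives S − P.

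**Four readings of the text**

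A. Costs are scenario totals, benefits are reductions against the status quo, and NSB is compared between scenarios.
- Status quo: 0 − L_sq.
- Dispensary: S − (L_d + P).
- Difference: S − L_d − P + L_sq = 2S − P.

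B. Costs are increments in every listed domain.
- Cost side: (L_d − L_sq) + P = P − S.
- NSB: S − (P − S) = 2S − P.

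C. Costs are totals, and NSB is reported for the dispensary model alone.
- NSB: S − (L_d + P). This lies below S − P by the whole residual burden L_d. Each further unit saved still moves it by 2.

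D. The cost side holds programme costs only, as in the opening sentence.
- NSB: S − P. Nothing is counted twice.

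**Illustration.** The units are assumed, not taken from the article: L_sq = 100 + 80 + 60 = 240 and P = 20.

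| Burden reduction | S | L_d | Single count (D) | A and B | C |
|---|---|---|---|---|---|
| 5% | 12 | 228 | −8 | 4 | −236 |
| 10% | 24 | 216 | 4 | 28 | −212 |
| 25% | 60 | 180 | 40 | 100 | −140 |

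**When the sign flips.** Under A and B a true loss (S − P < 0) is shown as a gain (2S − P > 0) exactly when S < P < 2S. The break-even programme cost moves from S to 2S. With the assumed P = 20, the sign flips for S between 10 and 20, that is, for burden reductions between 10/240 = 4.2% and 20/240 = 8.3%. The 5% row lies in that range; the 10% and 25% rows do not.

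**Benefits measured against the null scenario.** Let N be the burden there. If reductions are booked with their sign, NSB is (N − L) − (L + P) for each scenario, and the difference between dispensary and status quo is again 2S − P. But the null scenario has no enforcement and no treatment of use disorders, so the reductions in those two items against it are negative. If negative reductions are not booked as benefits, those items enter once only.

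**The case against.** The strongest reply is that the article does not prescribe double counting. It gives no equation, does not name the scenario against which reductions are measured, and does not say whether costs are totals or increments. Its opening sentence supports reading D, where nothing overlaps. In reading C the reported figure is too low, not too high. The article also condenses a full-length proposal that is not shown, and the missing equation and comparator may well be there.

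Much of this stands. A reader might infer that every saving is counted twice whatever is done; the text does not support that, because reading D is open. A reader might also infer that the doubling is the same whichever scenario is the reference; against the null scenario it is complete only if negative reductions are booked as benefits. Nor does it follow that the cost per DALY is wrong. The cost-utility analysis rests on the cost-benefit results, but the section does not say that the net figure is its numerator. A numerator of P − S, taken from the cost side alone, would double nothing.

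What does not stand is the defence that only detail is missing. The article states what goes on each side, and the lists overlap. Reading D requires setting aside most of the stated cost list. So the section either counts savings twice or contradicts its own first sentence, and it needs rewording in both cases.

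**Conclusion.** The concern holds in a limited form. The section places the same three domains on both sides, and this conflicts with its opening contrast. If costs are taken as scenario totals and the dispensary model is compared with the status quo, the difference in net social benefit is 2S − P instead of S − P. The overstatement is S, and the sign is wrong whenever S < P < 2S.

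The factor of two is algebraic and does not depend on the illustrative amounts. Whether the sign would change in practice depends on S and P, which the article does not give. The result also rests on a reading of comparator and cost totals that the text permits but does not fix.

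The consequence is confined to what the article calls an additional economic evaluation. The primary outcome, the secondary outcomes on cannabis use and the sample size are unaffected.

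**What to change.** Count each item once, against one named comparator. Either of two forms will do:

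1. Put only the costs of setting up and running the dispensary model on the cost side. Put the changes in enforcement, health-care and productivity costs, measured against the status quo, on the benefit side. This agrees with the opening sentence.
2. Compare total costs, including programme costs, between scenarios, with no separate benefit term.

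Write out the net social benefit equation for the chosen form, and state that the cost-per-DALY numerator follows the same single-count accounting.

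The cost is one reworded paragraph, with no new data and no change to the trial's conduct. The Ethical considerations section says ethical review has not yet taken place, so the correction can be made before the study starts.

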### Data collection and dissemination

Data collection will be completed using electronic means and all required measures will be implemented to protect the data and anonymity of all study participants at all times. In particular, the study will adhere to the European ‘General Data Protection Regulation’ (GDPR) according to which, health care data is particularly sensitive and should be handled with the greatest care. Further, cannabis possession will remain a federal crime, further emphasizing the sensitive nature of the study data. Thus, all data will be stored on hard drives encrypted using state-of-the-art encryption techniques (AES-256). Upon completion of the study, the study data will be kept on encrypted hard drives in physically locked cabinets.

Conditioned on the approval from the public study sponsor, all study data shall be made available to other researchers. All efforts will be undertaken to anonymize the study data (in the sense of GDPR) in order to publish the data in public repositories making the data findable, openly accessible, interoperable, and re-usable (FAIR principles issued by the European Union). Upon publication of the primary outcome analyses, study data shall be published alongside the respective code of the statistical programme. Through these means, we hope that our analyses will be reproducible and that the data will be used for other purposes than those described, increasing the merit of this study. Lastly, study results will be published under an open access licence to allow for a widespread recognition of our findings.

